# 1. Introduction

## 1.1. Background and rationale

See study protocol.

## 1.2. Objectives

The objective of this study is to analyse the feasibility and safety of Ultrasound-guided (US-G) Ventriculoperitoneal shunt (VPS) placement. The primary objective of the study is to compare the surgical intervention of VPS placement between US-G and stereotactic navigated placement plus additional 5 minutes.

The Null-hypothesis is that there are no differences in the surgical intervention time (plus additional 5 minutes in the stereotactic navigation group) between the two methods. The Alternative Hypothesis is that US-G VPS placement has a shorter surgical intervention time compared to stereotactic navigated VPS placement.

$$H_0: \text{Time}_{US-G} = \text{Time}_{\text{Stereotactic}} + 5\text{min}$$

$$H_1: \text{Time}_{US-G} < \text{Time}_{\text{Stereotactic}} + 5\text{min}$$

# 2. Study methods

## 2.1. Trial design

This study is a prospective randomized two-arms controlled superiority trial, conducted in a primary neurosurgical centre in Switzerland.

## 2.2. Randomisation

Randomisation will be performed by an independent individual using a stratified simple randomisation procedure as implemented in the electronic data capture software REDCap. An allocation ratio of 1:1 will ensure a balance in sample size across both groups over time. The randomisation will be stratified according to age of the patients (under 40 years/over 40 years).

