## 2.5. Stratification

Unless explicitly mentioned, analyses will not be stratified.

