### 6.3. Analysis methods

#### 6.3.1 Primary analysis

Analysis of the primary endpoint will follow the intention-to-treat (ITT) principle. It will be based on the FAS with missing data of the primary outcome imputed as described in the section “Missing data” (section 6.4). Patient data will be analysed according to their intervention allocation, irrespective of actual treatment received.

The primary outcome, surgical intervention time, will be assessed using a linear regression model. The estimates will be reported with 95% confidence intervals (CI). Explanatory variables will be BMI, underlying diagnosis, experience surgeon and the use of an old burr hole.

In case the outcome variable is not normally distributed, data will be transformed or a different model, depending on the distribution of the data, chosen.

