#### 6.4. Missing data

Missing baseline and outcome data will be summarized by study arm. As outlined above, the primary analyses will be the intent-to-treat population. In the case of missing data or drop-outs, we may adjust for further baseline variables which are associated with missing outcome data or we consider multiple imputation. Both, baseline patient characteristics and outcome variables will be considered for multiple imputations. Variables with more than 50% missing values will not be used for the imputation model. Categorical variables with a frequency of 5% or less in one category will also be omitted. Continuous variables will be imputed using linear regression and binary variables using logistic regression. We will construct and analyze 20 imputed data sets and combine results using Rubin's rules. Diagnostic checks, including model convergence and comparing observed versus imputed distributions, will be performed to ensure the quality of imputations.

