## **6.2 Methods of minimising bias**

### **6.2.1 Randomisation**

Randomisation will be performed by an independent individual using a stratified simple randomisation procedure as implemented in the electronic data capture software REDCap. An allocation ratio of 1:1 ensure a balance in sample size across both groups over time. The randomisation has been stratified according to age of the patients (under 40 years/over 40 years).

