#### **11.4.2 Primary Analysis**

The primary outcome, surgical intervention time, will be assessed using a linear regression model, reporting adjusted mean differences between arms. The estimates will be reported with 95% confidence intervals (CI). The model will be adjusted for the most important risk factors. Further details will be provided in the statistical analysis plan.

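### Age is the only randomisation stratum but is in none of the models, and the text on how allocation achieves balance contradicts itself; the consequence is modest and the repair cheap

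*Combined protocol and SAP*

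**What the plan says.** **Allocation.** Protocol 6.2.1 and SAP 2.2 both describe allocation "using a stratified simple randomisation procedure as implemented in the electronic data capture software REDCap". The only stratum is age: "The randomisation will be stratified according to age of the patients (under 40 years/over 40 years"). SAP 2.2 goes on: "An allocation ratio of 1:1 will ensure a balance in sample size across both groups over time". Protocol 6.2.1 makes the same claim in almost the same words. Neither document mentions blocks, a block size, minimisation or how the list was produced.

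**Analysis.** SAP 2.5: "Unless explicitly mentioned, analyses will not be stratified". No later section names an exception for age. For the primary model, SAP 6.3.1 says: "Explanatory variables will be BMI, underlying diagnosis, experience surgeon and the use of an old burr hole". SAP 6.3.1.2 uses the same four variables for the secondary outcomes, if numbers allow. Protocol 11.4.2 says only "The model will be adjusted for the most important risk factors" and leaves the detail to the SAP. The one route by which age could enter is optional and tied to missing data; in SAP 6.4, "we may adjust for further baseline variables which are associated with missing outcome data".

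**The concern.** Two things do not fit together.

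First, a 1:1 ratio fixes each patient's chance of either arm at one half. It does not make the arms equal in size; restricted allocation, such as permuted blocks, does that. Simple randomisation carried out separately within age strata produces the same distribution of arm sizes and age mix as simple randomisation with no strata. So the description promises a property that the named method does not have.

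Second, the one factor chosen for stratification is not used in the analysis, and no reason is given. A stratification factor normally goes into the model. If allocation was restricted on it, omitting it overstates the standard error. If allocation was not restricted, the model is the only place where a chance imbalance in age can be corrected.

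At stake are an accurate description of the design and some precision. The validity of the primary comparison is not.

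**Working it through.** **Inputs from the documents.** Difference 15 min, SD 28.65 min, 80% power, 58 per group before inflation, 1% drop-out, 5% non-adherence (SAP 2.3, protocol 11.2); two-sided 5% (SAP 4.2); total 130 in the SAP and 136 in the protocol. The documents give neither the share of patients under 40 nor the effect of age on surgical time. Both are assumptions below.

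**1. The plan's own figure.** n per group = 2(1.960 + 0.842)² × 28.65² / 15² = 57.3, so 58. Inflated: 58 / 0.99 / 0.95² = 64.9, so 65 per group. The SAP figure is reproduced.

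**2. Arm sizes if allocation is literally simple.** The size of one arm is Binomial(N, 0.5), whether or not patients are first split by age.

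| | N = 130 | N = 136 |
|---|---|---|
| Exactly equal arms | 7.0% | 6.8% |
| Expected absolute difference | 9.1 | 9.3 |
| Arms differ by 10 or more | 43.0% | 44.0% |
| Arms differ by 20 or more | 9.5% | 10.3% |
| Central 95% range, one arm | 54 to 76 | 57 to 79 |
| Smaller arm below 58 | 18.8% | 7.1% |

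**3. What unequal arms cost.** Power = Φ(15/SE − 1.96), with SE = 28.65 × √(1/n₁ + 1/n₂), for the full 15 min effect before drop-out and crossover, N = 130.
- 65:65: SE = 5.03, power 84.7%.
- 54:76: SE = 5.10, power 83.7%.
- Averaged over the binomial distribution: 84.4%.

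The average loss is about 0.3 percentage points, and about 1 point at the edge of the 95% range.

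**4. Age balance.** Assume 20% under 40, that is 26 of 130. Under simple allocation, 8 to 18 of them fall in a given arm (95% range). With the assumed share between 10% and 30%, the SD of the between-arm difference in that share is 5 to 8 percentage points, and a difference of 10 points or more occurs in 6% to 22% of trials. With permuted blocks of 4 within strata (block size assumed), the SD falls to 1.2 to 1.4 points, and no simulated trial reached 10 points.

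**5. What adjusting for age is worth.** Keep 20% under 40 and let age shift mean time by g minutes. Age then explains g² × 0.2 × 0.8 / 28.65² of the variance.
- g = 10: 16/820.8 = 1.9%; residual SD 28.37. Closed-form power at 65:65 goes from 84.7% to 85.4%. Simulated with unblocked allocation: 83.9% without age and 83.9% with it.
- g = 20: 64/820.8 = 7.8%; residual SD 27.51. Closed-form power goes from 84.7% to 87.5%. Simulated: 83.4% to 87.0%.

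The simulation standard error is about 0.4 points per figure, so the two methods agree on the order of size: a gain of under one point at 10 min, and about three at 20 min.

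**6. If the list was in fact blocked.** Leaving age out keeps its variance in the reported standard error although the design has removed it from the comparison. At g = 20 the standard error is too large by a factor of 28.65/27.51 = 1.04. Simulated type I error is about 4.2% (standard error about 0.4), against a nominal 5%. The error is on the conservative side.

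**The case against.** The strongest reply is that neither reading threatens the result. Simple randomisation is valid, and an unadjusted comparison after it is unbiased with correct type I error. If the list was blocked, the arms are balanced and omitting age is only slightly conservative. That stands, and it limits the weight of this point.

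Four stronger inferences are tempting, and the documents do not support them.

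- **That allocation was certainly unblocked, so stratification achieved nothing.** This is the literal reading of simple, but stratified simple pulls against itself, and a claim of balance over time fits restricted allocation better. The generation of the list is not described. The figures in steps 2 to 4 for simple allocation apply only if the literal reading is right.
- **That age is the factor the sponsor thought most important.** No section says so. Protocol 11.4.2 uses that kind of language for the model covariates, and the SAP then names four others.
- **That SAP 2.5 forbids age in the model.** It concerns stratified analyses and does not bar age as a covariate.
- **That a fixed number of patients is being wasted.** If age explained 5% to 10% of the variance, adjusting would be worth roughly 7 to 14 patients (130 × 0.05 = 6.5; 136 × 0.10 = 13.6). That share is assumed, and what counts is what age explains beyond the planned covariates. Protocol 3.1 links indication to age: normal pressure hydrocephalus in the elderly; haemorrhage, infection and trauma mostly in younger patients. Diagnosis, already in the model, may capture part of it.

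What the reply does not remove is that the allocation text cannot be right as it stands, and that the only stratum is left out of every model without explanation.

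**Conclusion.** The point holds as a modest one. Age is the sole stratification factor and is absent from the primary and secondary models; this follows directly from the text. The allocation description is inconsistent on either reading: if no blocks were used, the balance claim is false (a 43% chance of arms differing by 10 or more at N = 130) and stratifying has no effect on balance; if blocks were used, simple is the wrong word and the standard errors are slightly too large.

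There is no bias and no inflation of type I error. Unequal arms cost about 0.3 percentage points of power on average. The gain from adjusting ranges from almost nothing at a 10 min age effect to about three points at 20 min. It rests on an assumed 20% of patients under 40 and an assumed age effect, before any overlap with diagnosis. A reader who infers from the 43% that the trial is materially weakened would be going too far. The case for the change is that it is nearly free and brings the analysis into line with the design.

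**What to change.** 1. In SAP 6.3.1, add the age stratum, or age as a continuous variable, to the primary model. Do the same in SAP 6.3.1.2 where the number of events allows. State which form is used and, for the stratum, on which side a patient aged exactly 40 falls, since the two categories leave that open. Cost: one degree of freedom; age is already collected.
2. Fix this before outcomes are analysed by arm, so that adding age cannot look like a choice made on the results. SAP 2.5 need not be deleted; a cross-reference saying that age enters as a covariate is enough.
3. In SAP 2.2 and protocol 6.2.1, state how the REDCap list was generated. If no blocks were used, remove the claim that the ratio ensures balance. If blocks were used, replace simple with a description of permuted blocks within age strata.

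A new blocked list is probably not worth pursuing. Protocol version 3.4 is dated 20.08.2024, and the last participant is planned to leave in 02/2025 after a six-month visit, so on that plan enrolment ends at about the date of the protocol. Changing the allocation method would matter only if recruitment is still open.

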## 2.3. Sample size

The sample size was estimated with the aim of showing a surgical intervention time reduction of 15 minutes (min) in the intervention arm compared to the control arm. The significance level was chosen to be 5%, while the power was chosen to be  $(1-\beta) = 80\%$ .

Based on unpublished data from a pilot study assessing the surgical intervention time in patients undergoing VPS placement using US navigation, we calculated a mean surgical intervention time of 63 min with a standard deviation (SD) of 28.65 min. Because of the additional steps involved using stereotactically navigated surgery, we assume an increased surgical intervention time in those patients.

We then conservatively selected a scenario with a relatively modest difference between groups. This resulted in 58 patients with VPS placement surgery per group. Anticipating a 1% drop-out by deaths and a surgeons' non-adherence rate (change from control to treatment arm) of 5%, a total sample size of 130 patients (65 per group) was required.

## 2.4. Framework

All endpoints will be analysed for the superiority of US-G VPS placement compared to stereotactic navigated VPS placement.

## 2.5. Stratification

Unless explicitly mentioned, analyses will not be stratified.

## 2.6. Statistical interim analyses and stopping guidance

No interim analysis planned.

# 3. Data management

## 3.1. Data export

The entered data will be exported from the trial database (REDCap) to a statistical software package.

## 3.2. Data validation

Data validation and cleaning will be conducted after completion of data entry but before database lock.

# 4. Statistical principles

## 4.1. General

All recorded and derived variables will be presented by intervention group (and visits, if appropriate) using descriptive summary tables. Continuous variables will be summarised by mean and standard deviation, or median and quartiles. Categorical variables will be summarised with absolute and relative frequencies.

## 4.2. Confidence intervals and p-values

The statistical testing will be two-sided with a significance level of 5%. All tests will be accompanied by an effect measure with a 95% confidence interval (95% CI).

## 4.3. Adherence and protocol deviations

Substantial amendments are changes that affect the safety, health, rights and obligations of participants, changes in the protocol that affect study objective(s) or central research topic, changes of study site(s) or of study leader and sponsor (ClinO, Art. 29).

## 4.4. Analysis populations

The population for analysis will comprise all patients as randomized and with completed follow-up (no drop-outs), hence the full analysis set (FAS). All statistical analyses will be performed on the FAS according to the intention-to-treat principle (i.e. all participants will be analysed on the basis of the intervention to which they were randomly allocated).

The per-protocol (PP) set will include all participants in the FAS who fulfilled the eligibility criteria, for whom the surgery was completed as planned in the study protocol, and for whom the measurement of the primary outcome is available.

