##### 6.3.1.2. Analysis of secondary outcomes

All analysis of the secondary endpoints will follow the intention-to-treat (ITT) principle. It will be based on the FAS with missing data of the primary outcome imputed as described in the section “Missing data” (section 6.4).

The continuous secondary endpoints (outcomes operation time, anaesthesia time, volumetry of side ventricles, and Evan’s Index) will be assessed using linear regression models, the binary endpoints (optimal catheter placement, complications, mortality and revision surgery) will be assessed using logistic regression, and the number of puncture attempts will be assessed using a poisson regression model.

All estimates will be reported with 95% CI. IF numbers allow explanatory variables will be BMI, underlying diagnosis, experience surgeon and the use of an old burr hole.

In case the outcome variable is not normally distributed or model assumptions are violated, data will be transformed or a different model, depending on the distribution of the data, chosen.

Deviation from the original statistical plan:

If substantial deviations of the analysis as outlined in these sections are needed for whatever reason, the protocol will be amended. All deviations of the analysis from the protocol or from the detailed analysis plan will be listed and justified in a separate section of the final statistical report.

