#### 6.5. Evaluation of safety parameters

Evaluation of safety parameters will be based on the safety population (FAS, section 4.4). They will be listed according to the treatment the patient actually received with the time points of onset. If many adverse events should be observed, we will compare frequency between treatment groups.

Safety endpoints are the following events: positioning of the catheter, number of ventricle puncture attempts, VPS dysfunction, revision rate, perioperative complications (bleeding, infection), complications due to head clamp, death, and coma.

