The second follow-up will be performed 6 months postoperatively and includes a cCT scan (catheter position (optimal vs. not optimal, grade I to IV), calculation of Evans' index, volumetry of side ventricles), neurologic examination (analysis of GCS, modified Rankin Scale (mRS), Glasgow Outcome Scale (GOS), and neurological symptoms (headaches, vomitus, gait disturbances, urinary incontinence, dementia, coma, delir)), analysis of postoperative complications (bleeding, complications due to head clamp, VPS infections, death), and type and reason for revision surgery.

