### 7.4 Criteria for withdrawal/discontinuation of participants

Patients will be withdrawn from the study in case of withdrawal of informed consent or non-compliance, as well as patients with VPS dysfunction receiving revision surgery on the same side and location. If the surgeon shows non-adherence to the allocated navigation method (estimated in 1% of all cases), the patient will also be included, but will be included in the as treated analysis. Patients will not be replaced.

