#### **11.4.1 Datasets to be analysed, analysis populations**

The full analysis set (FAS) will include all patients that were randomized. All statistical analyses will be performed on the FAS according to the intention-to-treat principle (i.e. all participants will be analysed on the basis of the intervention to which they were randomly allocated).

The per-protocol (PP) set will include all participants in the FAS who fulfilled the eligibility criteria, for whom the surgery was completed as planned in the study protocol, and for whom the measurement of the primary outcome is available.

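### The SAP limits the full analysis set to patients with completed follow-up, against the protocol's all-randomised definition; read literally, it would bias the mortality, revision and safety analyses

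*Combined protocol and SAP*

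**What the plan says.** The two documents define the same set differently.

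- Protocol 11.4.1: "The full analysis set (FAS) will include all patients that were randomized".
- SAP 4.4: "The population for analysis will comprise all patients as randomized and with completed follow-up (no drop-outs), hence the full analysis set (FAS"). The next sentence adds: "All statistical analyses will be performed on the FAS according to the intention-to-treat principle".

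SAP section 7, on changes from the protocol, records none.

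The SAP definition reaches every analysis. SAP 6.3.1 bases the primary analysis on the FAS. SAP 6.3.1.2 does the same for the secondary outcomes, where "the binary endpoints (optimal catheter placement, complications, mortality and revision surgery) will be assessed using logistic regression". For safety, SAP 6.5 says: "Evaluation of safety parameters will be based on the safety population (FAS, section 4.4"). The only other set, the per-protocol set, is a subset of the FAS.

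Three further places bear on who counts as a drop-out. SAP 2.3 inflates the sample size with the words "Anticipating a 1% drop-out by deaths". Protocol 7.4 lists among the patients to be withdrawn those who withdraw consent or do not comply, "as well as patients with VPS dysfunction receiving revision surgery on the same side and location". Protocol 6.1 sets the end of follow-up: "The second follow-up will be performed 6 months postoperatively".

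**The concern.** Membership of the SAP set is decided after randomisation, by what happens over the following six months. For mortality and revision, what happens is the endpoint itself: a death, or a same-site revision that triggers withdrawal, can remove the patient from the analysis meant to count it. The safety population inherits the same condition. An analysis on such a set is not intention-to-treat, whatever it is called.

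The primary outcome needs no follow-up after surgery, because surgical intervention time is recorded on the operation day (protocol 9.2.1 and 9.3.2). A completed-follow-up rule therefore drops valid primary values because of later events.

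The SAP also leaves the choice of patients open. An analyst who follows 4.4 and one who follows 6.4 would analyse different patients, and the choice could be made after the data are seen.

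**Working it through.** **1. The passages side by side**

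| Place | What it implies for a patient who does not reach the 6-month visit |
|---|---|
| Protocol 11.4.1 | In the FAS, because randomised |
| SAP 4.4, first sentence | Not in the FAS, if follow-up counts as incomplete |
| SAP 4.4, second sentence | Intention-to-treat, so analysed as allocated |
| SAP 6.3.1 | FAS, with missing primary outcomes imputed |
| SAP 6.4 | Extra covariate adjustment or multiple imputation if there are drop-outs |
| SAP 6.5 | In the safety population only if in the SAP 4.4 set |
| SAP section 7 | No departure from the protocol |

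The first sentence of SAP 4.4 is the outlier. It conflicts with the protocol, with the sentence after it, and with the missing-data plan.

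**2. Which events the literal reading removes**

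- *Deaths.* SAP 2.3 calls deaths drop-outs, and SAP 4.4 admits no drop-outs. At the documented 1%, expected deaths are 0.01 × 130 = 1.3 at the SAP's total and 0.01 × 136 = 1.36 at the protocol's.
- *Same-site revisions for dysfunction.* Protocol 7.4 withdraws these patients. Protocol 8.5 then follows withdrawn patients as non-participants, so their study follow-up is not complete in the ordinary sense. Revision surgery is a secondary outcome, and dysfunction and revision rate are safety endpoints. The documents give no expected rate, so this loss cannot be sized.
- *Other losses.* Complications seen before a patient was lost would go as well.

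**3. Cost to the primary analysis**

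Inputs from SAP 2.3 and 4.2: difference 15 min, SD 28.65 min, two-sided 5%, power 80%, loss 1%, change from control to treatment arm 5%. Group sizes: 65 (SAP 2.3) and 68 (protocol 11.2).

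The plan's own figure first. Per group,

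n = 2 × [28.65 × (1.960 + 0.842) / 15]² = 57.27, rounded up to 58, as stated.

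Inflating, 58 / (0.99 × 0.95²) = 64.9, which gives 65 per group and 130 in total, as in the SAP.

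Now the effect of removing non-completers. With 5% one-way crossover the difference is diluted to 15 × 0.95 = 14.25 min. Power is that of a two-sample t-test with n(1 − loss) per group and noncentrality (14.25 / 28.65) × √[n(1 − loss) / 2].

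| Loss before 6 months | Power from 68 per group | Power from 65 per group |
|---|---|---|
| 0% | 82.1% | 80.4% |
| 1% (documented) | 81.7% | 80.0% |
| 10% (assumed) | 77.9% | 76.0% |
| 15% (assumed) | 75.5% | 73.6% |
| 20% (assumed) | 72.9% | 71.0% |

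The 0% row already carries the crossover dilution, so differences from it are due to the exclusion alone. At 1% the cost is 82.1 − 81.7 = 0.4 points, and likewise 80.4 − 80.0 = 0.4.

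**The case against.** The strongest reply is that the SAP does not clearly intend a completers-only analysis. It never defines completed follow-up, and a patient observed until death can be said to have been followed completely. The only text linking death to drop-out is a sample-size allowance, which is not a rule for forming an analysis set. The SAP makes mortality an endpoint and lists death under safety, which would be pointless if deaths were excluded. SAP 6.3.1 and 6.4 plan imputation or adjustment for drop-outs, and SAP 5.4 lists every withdrawal and loss with time and reason, so these patients would be disclosed in any case.

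Much of this stands. A reader might infer that the SAP guarantees zero deaths in both arms whatever happens. The documents do not support that: it is the outcome of one literal reading of an undefined term, and other sections point the other way. A reader might also infer that the primary comparison is biased or underpowered. Nothing in the documents shows that later loss depends on operation-day surgical time, and every power figure below 80% in the table comes from a loss rate the documents do not give.

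The reply does not remove the conflict. The two FAS definitions cannot both hold, the narrower one is undeclared, and whether deaths and revisions are counted should not depend on how an undefined term is read. That SAP 6.3.1 and 6.4 seem to keep drop-outs makes the correction uncontroversial; it does not make SAP 4.4 right.

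**Conclusion.** SAP 4.4 is wrong as written. It contradicts protocol 11.4.1, the intention-to-treat principle it invokes, SAP 6.3.1 and 6.4, and the declaration in SAP section 7. If followed literally, it would exclude deaths, losses and withdrawals before 6 months from the analyses of mortality, revision, complications and safety, and would discard recorded primary outcomes.

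The main harm is bias in mortality, revision and safety. About 1.3 to 1.4 deaths are expected at the documented 1%, so the absolute number is small, but with so few events each one matters. The loss of same-site revisions could be larger; the documents do not allow an estimate. The power cost at 1% is about 0.4 points and would not by itself justify a change.

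The conclusion rests on two readings: that a patient who dies, or is withdrawn under protocol 7.4, counts as a drop-out or as not having completed follow-up. Both are the natural reading of the text, but the SAP states neither as an analysis rule. The contradiction between the two FAS definitions needs no such assumption.

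**What to change.** - **SAP 4.4.** Replace the first sentence with the protocol definition: all randomised patients, analysed as allocated.
- **SAP 6.3.1.** State that every recorded surgical intervention time enters the primary analysis regardless of later follow-up. Randomised patients with no recorded time, including any not operated on, are handled under SAP 6.4.
- **SAP 6.5.** Define the safety set as all operated patients, with no follow-up condition. Count deaths, and revisions that lead to withdrawal, as events.
- **SAP 6.3.1.2.** Apply the same event rule to mortality, revision and complications. State how the logistic models treat patients who leave early without an event.
- **SAP 6.4 and section 7.** Align the missing-data wording with the restored FAS, and make section 7 true of the final text.

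The cost is a few sentences in the SAP, best settled before the analysis. No new data are needed, since surgical times are recorded at operation and a revision that leads to withdrawal is known when it happens. The target sample size does not change.
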